### Demographic and anthropometric information

During baseline testing the participants will complete a patient demographics form, which will provide information regarding patient medical history, comorbidities, medications, and personal factors (e.g., history of falls, exercise status). They will also complete information related to the medical history such as the sequence of symptoms that lead to their diagnosis of specific Multiple Sclerosis (MS). We will also record questions regarding their current management of MS symptoms, such as medications, physical therapy, and other treatments.

### Measures of body structure and function

*Video Head Impulse Test (vHIT)* is a measure of gaze stability indicated by the strength of the vestibulo-ocular reflex (VOR) in each of the six semicircular canals. vHIT testing will be performed using the Otometrics ICS impulse system (Natus Medical Inc.). This system quantifies VOR function by calculating the ratio between eye and head velocity, known as VOR gain during low amplitude, moderate velocity, and high acceleration head impulses performed by the examiner. Higher gains indicate better performance with healthy control gain values provided by the manufacturer (VOR gain typically > 0.8 are normal) [22, 23]. Additionally, data regarding the positional error of the eye in relation to the head will be calculated as will various metrics of saccade behavior (i.e. latency, amplitude, and frequency) [24–26]. Testing of VOR function with vHIT is more reliable than clinical non-instrumented head impulse testing and has been used extensively in assessing vestibular function in a variety of diagnoses [27]. Additionally, vHIT testing is validated in PwMS to have significantly more pathological VOR gains compared to healthy controls [28](Table 3).

**Table 3 Tab3:** Outcome measures utilized in study showing their collective representation of ICF domains

ICF Disablement Construct	Outcome Variable
Body Structure and Function	video Head Impulse Test (vHIT)
	Reactive Stepping
Activity	Dynamic Visual Acuity (DVA)
	Mini-BESTest
	Functional Gait Assessment (FGA)
Participation	Dizziness Handicap Inventory (DHI)
	Activities-Specific Balance Confidence Scale (ABC)
	VAS of Global Dizziness and Balance

*Reactive stepping* is the response to a random perturbation or release causing a quick, highly integrated postural response to recover equilibrium and functions as a measure of postural stability and the VSR [29]. In this study reactive stepping will be performed using a backwards tether release paradigm, during which participants will be asked to lean backward against a force detecting tether until in a range of 8–12% of body weight. When in this range, the tether will randomly release and measures of the latency of the first step, length of the step, and the margin of stability will be captured using 3D motion capture. Previous research has demonstrated that PwMS had larger center of mass displacements and step latencies than healthy controls during a similar corrective stepping task and the magnitude of these deficits significantly correlated to increased severity on clinical outcome measures [29, 30](Table 3).

### Measures of activity

*Dynamic Visual Acuity (DVA)* is a functional assay of the VOR and measures visual acuity during self-generated head rotation. DVA is measured using a head worn accelerometer and a tablet computer (Table 3).

*The Mini BESTest* measures postural stability performance during static, dynamic, and reactive balance activities designed to target 6 different balance control systems. The Mini BESTest has high content validity with gold standard measures of balance deficits such as Berg Balance Scale, Clinical Test of Sensory Integration in, Balance, Dynamic Gait Index, and Timed Up and Go (TUG) test [31]. Studies comparing the Berg Balance Scale to the Mini BESTest, found that the Mini BESTest had a lower ceiling effect and higher values on responsiveness tests, suggesting it may be more sensitive to detecting changes in balance in PwMS who display minimal walking disability [32] (Table 3).

*The Functional Gait Assessment (FGA)*(Primary Outcome) is a commonly used 10 item assessment of dynamic postural stability consisting of a variety of ambulatory tasks including normal walking, walking with head turns, stepping over obstacle, stopping and turning, walking with a narrow base of support, and ascending/descending stairs, among others. The FGA has excellent concurrent validity when compared to the Berg Balance Scale, timed up and go to TUG, and Activities-specific Balance Confidence Scale in many populations who are known to have balance deficits including Multiple Sclerosis, Parkinson’s disease, older adults, vestibular disorders, and stroke [33–35] (Table 3).

### Measures of participation

The *Dizziness Handicap Inventory (DHI)* (Primary Outcome) is a 25 item self-reported questionnaire chosen to examine disability related to gaze instability that evaluates individual perceptions of the impact of dizziness and/or unsteadiness on functional and participation level activities. The questionnaire requires participants to determine if an activity/event never, sometimes, or always causes an increase in dizziness or unsteadiness. Total scores range from 0 to 100, with higher values indicating greater dizziness related disability [36, 37]. The DHI has adequate to excellent correlation with the Berg Balance Scale and the Dynamic Gait Index in PwMS [38, 39] (Table 3).

*Activities-Specific Balance Confidence Scale (ABC)* is a 16 item self-reported measure of postural stability that quantifies the individual’s confidence and/or self-efficacy in performing various dynamic or static activities. Questions require participants to rate their confidence in performing each activity without a loss of balance or a fall from 0 to 100%, with 100% indicating total confidence. The ABC has been validated in PwMS finding concurrent convergent validity was moderate to good (0.50 to − 0.75) with the highest correlation for the 12 item MS walking scale [40, 41] (Table 3).

*Visual Analog Scale of Global Dizziness and Balance* is an analog scale used to rate global intensity of dizziness and balance over the last 48 h. The individual will mark a vertical oriented line on a 10 cm line to indicate the amount of dizziness or unsteadiness they are feeling. The start of the line indicates no symptoms and the end of the 10 cm line indicates the most dizziness or unsteadiness they can experience. Similar scales have been used to measure global pain ratings [42, 43], to quantify visual vertigo [44], and rate the severity of dizziness and unsteadiness [45, 46] (Table 3).

### Controls for threats to internal validity

Additionally, the following measures will be collected as they could have an influence on the dependent measures, but are not considered primary or secondary outcome measures.

*Expanded Disability Status Scale (EDSS)* The EDSS is a valid and reliable indicator of disability used by referring medical providers in PwMS. While we do not expect the EDSS to change as a result of our intervention, these scores are important to characterize the sample of participants and may be important co-variates in our statistical analysis. EDSS scores will be gathered by a trained rater [47].

*Six Minute Walk Test (6MWT)* The distance walked during the 6MWT is a valid and reliable measure of locomotor ability in populations with a variety of chronic diseases including MS. [48] Higher values reflect greater ability. To perform this test, participants will circle a 25-m course continually for 6 min according to the standardized protocol described by the American Thoracic Society [49]. We have previously used this measure with PwMS to examine ambulatory ability using in-clinic and with wearable monitors which measured community ambulatory activity [50, 51].

*Modified Fatigue Impact Scale (MFIS)* The MFIS contains 5 statements that describe how fatigue may impact an individual with MS during the previous 4 weeks. Each item is rated on a 5-point ordinal scale; total scores range from 0 to 20, and lower scores indicating less fatigue. The MFIS has been validated previously as a measure of fatigue in individuals with MS. [52]

*Fatigue Severity Scale (FSS)* The FSS is a 9-item questionnaire commonly used in examination of fatigue in Multiple Sclerosis [53]. It uses a 7 point Likert scale in which users are asked to rate how strongly they agree with a statement pertaining to how fatigue has influenced their life in the last week. Scores range from 9 (lowest fatigue) to 63 (highest fatigue).

### Measures of intervention integrity and compliance

In order to quantify the dosage and progression of the head and trunk movement exercises performed during the intervention period and to confirm that the groups differed in this regard, we will utilize wearable inertial measurement units (IMU) during treatment and track progression with daily notes and participant recorded home exercise logs. At three points over the course of treatment the treatment period (approximately treatment 1, treatment 9, and treatment 18) participants will wear a suite of three IMU sensors placed on the forehead, sternum, and low back. (APDM inc. Opal) While wearing the sensors, the participants will complete their daily exercise routine and data regarding the direction, amplitude, frequency, and velocity of head and trunk turns will be captured. Concurrently, the research staff delivering treatment will track exercises performed, duration, intensity. This will allow us to 1) track progression of vestibulo-ocular reflex exercises in the GPS group, 2) compare the overall magnitude of head movement during treatment between the GPS and SOC groups, and 3) track the progression of aerobic and resistance training exercises in both groups.

Daily notes and home exercise logs will be collected for both groups to determine daily progression of all exercises and to measure compliance to the treatment protocol and home-based exercise prescription. Measures of progression and compliance may serve as important modifying variables in the final analysis.

### Statistical analysis plan

All data will be initially analyzed to determine if assumptions for parametric analysis are met. Decisions regarding appropriate statistical tests will be made based on the normalcy of the data. Corrections for increased type 1 error risk will be performed separately for the data within each specific aim. Post-hoc power and effect size will be calculated for all tests to inform the sample sizes of future studies.

Analyses of longitudinal outcomes will be performed using mixed effects models in which results are robust to missing data as long as the pattern of missingness conforms to the missing at random (MAR) assumption [54]. If more than 10% of follow-up measurements are missing for primary or any of the main secondary outcomes at any of the follow-up visits, sensitivity analyses will be performed after applying multiple imputation to impute missing data under models incorporating predictors of missingness and/or the outcome variables [55].

For the primary outcomes (DHI and FGA) we will apply a linear mixed model [55] to compare mean scores at the post-test and follow-up assessments between the GPS and SOC groups after controlling for baseline scores. Statistical inferences will be performed using restricted maximum likelihood estimation under an unstructured covariance model to account for serial correlations among repeated measurements. The fixed effects terms will include the baseline scores, follow-up visit (as a categorical variable), treatment assignment, and the interaction between follow-up visit and treatment assignment. For secondary outcomes, similar mixed effects analyses will be applied to evaluate the effects of the GPS intervention compared to SOC on the ABC, Mini-BESTest, DVA, vHIT, and reactive postural response tests, adjusting in each case for initial levels of the dependent variable. Monitoring for safety will be conducted throughout the study, investigating all possible unanticipated safety events.

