**Methods/design:**

The study is a single blind RCT designed to examine the benefit of a gaze and postural stability (GPS) intervention program compared to a standard of care (SOC) rehabilitation program in dizzy and balance impaired PwMS. Outcomes will be collected across the domains of body structure and function, activity, and participation as classified by the World Health Organization International Classification of Functioning, Disability, and Health (ICF). Our primary outcomes are the Dizziness Handicap Inventory (DHI) and the Functional Gait Assessment (FGA). Secondary outcomes include other measures of gaze and postural stability, fatigue, and functional mobility. Participants who are interested and eligible for enrollment will be consented prior to completing a baseline assessment. Following the baseline assessment each participant will be randomized to either the GPS or SOC intervention group and will complete a 6 week treatment period. During the treatment period, both groups will participate in guided exercise 3x/week. Following the treatment period participants will be asked to return for a post-treatment evaluation and again for a follow-up assessment 1 month later. We anticipate enrolling 50 participants.

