Recently published studies have taken critical first steps in exploring the use of vestibular based rehabilitation in patients with MS who have complaints of dizziness and poor balance [8, 9]. These studies demonstrated significant improvements in outcomes including patient reported dizziness and scores of the sensory organization test following participation in a vestibular based rehabilitation protocol. To expand on this work, we have designed the current study to examine the use of a vestibular rehabilitation protocol to improve self-reports of dizziness handicap, dynamic stability during gait, as well as gaze and postural stability outcomes. The measures used in this study were chosen to reflect domains of disablement from across the spectrum of the World Health Organization International Classification of Functioning, Disability, and Health (ICF) [10]. Specifically, the outcomes in the domain of body structure and function are measures of the vestibulo-ocular reflex (gaze stability) and the vestibulo-spinal reflex (postural stability). The Activity domain is measured by examining each participant’s ability to stabilize vision during movement and maintain postural stability during various tasks. Participation will be examined using questionnaires pertaining to limitations during life situations as a result of poor gaze and/or postural stability.

The purpose of this manuscript is to summarize the protocol (study design, participants, outcome measures, intervention details, and planned statistical analysis) to be used in a prospective randomized clinical trial (RCT). The objectives of this RCT will be to (1) characterize baseline gaze and postural stability limitations across the domains of the ICF in individuals with MS, and (2) to systematically test the efficacy of a vestibular rehabilitation approach at improving gaze and postural stability in individuals with MS compared to a standard of care intervention.

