### Power/sample size calculation

Using data from: 1) our pilot research on gaze and postural stability in persons with MS [8] and 2) spatial and temporal measures from previous vestibular research examining the response to task specific training [11–14], we estimated an effect size of d = 0.25 for the DHI with the correlation between baseline and follow-up measurements as 0.50. Twenty participants in each arm provides us with greater than 80% power and 2-sided α = 0.05 to detect a difference between groups on the DHI. We will enroll 50 individuals with MS from various sources to ensure adequate power to examine both DHI and FGA.

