## Discussion

Dizziness and falls are among the most debilitating symptoms reported by people with MS. [5] While a number of studies have attempted to improve balance in people with MS [56, 57] it was not until recently that management of balance and dizziness have been approached using a vestibular rehabilitation perspective [8, 9]. To further explore this innovative rehabilitation approach, we have designed this intervention trial to examine the use of vestibular rehabilitation using a randomized controlled trial design. Outcomes being explored have been categorized as either relating to gaze (dizziness) or postural (balance) stability. Furthermore, we have made it a goal to explore outcomes across the spectrum of disability as defined by the WHO International Classification of Functioning, Disability, and Health. This includes outcomes from the domains of Body Structure and Function, Activity, and Participation related to both gaze and postural stability. The results from this study will significantly add to the literature surrounding the impact and recovery of dizziness and balance impairment in people with MS and ultimately lead to improved rehabilitative management for these people.

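### The error rate across the two primary outcomes is undetermined, because the correction unit is never listed and no primary visit or success rule is named; power uses an uncorrected 0.05 for DHI alone

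*Protocol article*

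**What the plan says.** The Abstract and the outcome descriptions designate both DHI and FGA as primary. They give no order between them and do not say whether one or both must be positive.

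The Statistical analysis plan section applies a linear mixed model to each outcome "to compare mean scores at the post-test and follow-up assessments between the GPS and SOC groups after controlling for baseline scores". Its fixed effects include "the interaction between follow-up visit and treatment assignment", so each visit has its own treatment effect. The same section states the multiplicity rule: "Corrections for increased type 1 error risk will be performed separately for the data within each specific aim".

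No specific aims are listed. The Background gives two objectives: a baseline characterisation, and an efficacy objective, "to systematically test the efficacy of a vestibular rehabilitation approach at improving gaze and postural stability in individuals with MS". The Discussion offers another grouping: "Outcomes being explored have been categorized as either relating to gaze (dizziness) or postural (balance) stability".

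The Power/sample size calculation section assumes an "effect size of d = 0.25 for the DHI", a baseline-to-follow-up correlation of 0.50, 20 per arm and two-sided alpha 0.05, and claims more than 80% power. It then says: "We will enroll 50 individuals with MS from various sources to ensure adequate power to examine both DHI and FGA".

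**The concern.** Two outcomes at two visits give four between-group contrasts, and any of them could be presented as the primary result. The article does fix a correction rule, but the unit of that rule is not identified, and the groupings it offers lead to different places:

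- **Aims follow the objectives.** Both primaries fall under the efficacy objective and are corrected against each other, but in the same family as ABC, Mini-BESTest, DVA, vHIT and reactive stepping. Nothing protects the primary tests from the number of secondary ones.
- **Aims follow the gaze/posture split.** The article describes DHI as a measure of disability from gaze instability and FGA as a measure of dynamic postural stability. The two primaries then sit in different families and are never corrected against each other.

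The power statement also conflicts with the correction rule. It spends the full 0.05 on DHI, while the analysis section promises a correction that would, on the first reading, leave less than that. The claim about FGA has no input behind it. At stake are the false-positive rate of a claim of efficacy and the credibility of the stated power.

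**Working it through.** **Inputs from the article:** 2 primary outcomes, 2 visits, 20 per arm, 50 enrolled, two-sided alpha 0.05, r = 0.50, d = 0.25 for DHI. **Assumed:** equal arms (25 per arm if all 50 complete); Bonferroni as the within-family correction; visit correlation 0.5–0.8 and outcome correlation 0–0.5 between test statistics. The article states none of these assumptions.

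**1. The plan's own power figure.** With ANCOVA the residual SD is √(1 − 0.5²) = 0.866, in units of the outcome SD. The noncentrality is (0.25/0.866) × √(20/2) = 0.913. Noncentral t gives 14% power at two-sided 0.05, so the stated figure of more than 80% is not reproduced. It is reproduced if 0.25 is Cohen's f for a group-by-time interaction with two time points and correlation 0.5: 86.9% with 40 participants. The article calls it d.

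**2. Familywise error across the primaries under each reading.**

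| Reading | Error rate |
|---|---|
| Efficacy objective is one aim, all contrasts corrected together | at most 5% |
| Gaze/posture split, each outcome corrected across its two visits (each test at 0.025) | 7.4% (visit 0.8, outcome 0.5) to 9.1% (visit 0.5, outcome 0) |
| Two outcomes at one visit, no correction between them | 9.1% (outcome 0.5) to 1 − 0.95² = 9.75% (independent) |

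The second row, and the 9.1% in the third, come from simulation of correlated normal statistics (1,000,000 draws).

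**3. Size of the shared family on the first reading.** Two primary and five named secondary outcomes at two visits give 7 × 2 = 14 contrasts. There are more if the several vHIT and stepping metrics count separately.

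**4. Detectable effect with 80% power** (noncentral t, ANCOVA, r = 0.5, in outcome SDs).

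| Completers per arm | alpha 0.05 | alpha 0.025 |
|---|---|---|
| 20 | 0.79 | 0.87 |
| 25 | 0.70 | 0.78 |

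An effect of 0.79 SD, which has 80% power at 0.05 with 20 per arm, has about 70% at 0.025. With 25 per arm the same effect has 81% at 0.025 and 73% at 0.0125.

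**5. FGA.** No effect, SD or correlation is given, so no power can be computed for it.

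**The case against.** The strongest reply is that the article claims no familywise rate, so none can be shown to be breached. The only enumerated goals are the two objectives, and the natural reading puts both primaries and both visits under the efficacy one. The gaze/posture split rests on a Discussion sentence that sorts outcomes and does not define aims; the same paragraph also sorts them by ICF domain. A condensed article may well leave the list of aims and the correction method to a full protocol or SAP. On power, enrolling 50 rather than 40 offsets a two-outcome Bonferroni correction: 0.78 SD at 0.025 with 25 per arm is slightly better than 0.79 SD at 0.05 with 20.

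Much of this stands. The error rate is undetermined, not shown to be inflated. The unnamed correction method is not a finding in itself.

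Two stronger readings should be resisted. A reader might infer a familywise error of 14–17% from four uncorrected contrasts. That assumes no correction at all, which the quoted rule contradicts. A reader might also infer that the primaries lose about half their power. That figure (80% falling to 42%) needs Bonferroni over 14 contrasts with only 20 per arm, and a benchmark of 0.79 SD that is not the article's d = 0.25. With 25 per arm it is 56%, and the article names neither Bonferroni nor a family of 14.

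What the reply does not answer is that the article commits to a family that either pools the primaries with the secondary outcomes or leaves them uncorrected against each other, and that it computes power at an alpha which its own rule may not leave available. The offset from 40 to 50 holds only if nearly all complete (24 per arm gives 79%) and says nothing about FGA.

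**Conclusion.** The point holds as a defect of specification. The primary familywise error lies anywhere from at most 5% to about 7–9% according to how the aims are drawn, and reaches 9–10% for the two outcomes at one visit with no correction between them. The 7–9% range rests on the assumed correlations and on Bonferroni across visits; the 5% bound rests on a method that controls familywise error. If both outcomes were required for success, no correction between them would be needed. Joint power would then be lower, for example 0.8 × 0.8 = 64% with independent tests at 80% each. This is why the success rule matters.

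The power statement is inconsistent with the promised correction, and the FGA claim is unsupported. Multiplicity is not, however, what breaks the stated power: d = 0.25 as written gives about 14% even at 0.05. If 0.25 is really f for the interaction with two time points, 50 completers keep 88.5% at 0.025 and 82% at 0.0125.

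**What to change.** - Name one primary visit for both DHI and FGA, for example the 6-week contrast from the mixed model. The article does not compel that choice; what matters is that one is fixed.
- State the success rule. If either outcome suffices, control familywise error at 0.05 across the two with Holm.
- Put the 10-week contrasts and the secondary outcomes in a separate family tested afterwards, and replace the correction by specific aim with this rule.
- Restate power or the detectable effect at alpha 0.025, identifying whether 0.25 is d or f and for which test.
- Give an FGA effect and SD, or delete the claim of adequate power for both outcomes.

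The change is to wording only. The Data Availability statement says that data are still being collected and remain blinded, so it can be made before unblinding. The statistical cost is a less favourable detectable effect for the smaller p-value: 0.79 to 0.87 SD with 20 per arm, or 0.70 to 0.78 SD with 25. Holm tests the second outcome at the full 0.05 once the first is rejected.

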## Methods/design

Study design: The proposed project is designed as a single blind RCT. Participants in the trial will be tested at baseline, 6-weeks (post-intervention), and 10-weeks (follow-up). The intervention period lasts for a total of 6 weeks over which participants in both control and intervention groups participate in 18 visits of guided treatment at a frequency of 3x/week. (Fig. 1).

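### The primary mixed model has no baseline × visit term, so one baseline slope must serve both the 6-week and the 10-week score; adding the term is a cheap, minor improvement

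*Protocol article*

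**What the plan says.** All of this stands in the Protocol article, section Statistical analysis plan, unless another section is named.

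- The aim of the primary model is to "compare mean scores at the post-test and follow-up assessments between the GPS and SOC groups after controlling for baseline scores". There are two post-baseline visits, at 6 and 10 weeks (Methods/design).
- The mean model is given as a list: "The fixed effects terms will include the baseline scores, follow-up visit (as a categorical variable), treatment assignment, and the interaction between follow-up visit" and treatment. The only interaction with visit is the one with treatment.
- Estimation is by "restricted maximum likelihood estimation under an unstructured covariance model to account for serial correlations among repeated measurements".
- Secondary outcomes get similar models, each adjusted for its own baseline.
- On missing data, the section says of mixed models that "results are robust to missing data as long as the pattern of missingness conforms to the missing at random (MAR) assumption". If more than 10% of values are missing at a follow-up visit, "sensitivity analyses will be performed after applying multiple imputation to impute missing data under models incorporating predictors of missingness".
- The Power/sample size calculation section takes "the correlation between baseline and follow-up measurements as 0.50", a single value that is not split by visit.

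**The concern.** With baseline entered once and not crossed with visit, one coefficient links baseline to both follow-up scores. The covariance part of the model leaves the two visit variances and their correlation free, yet the mean part holds the baseline association equal at the end of treatment and four weeks later. The article gives no reason for freeing the one and fixing the other.

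Two things are at stake. If the slopes differ, adjustment at each visit uses the wrong slope, which wastes some of the precision that baseline adjustment should bring. Likelihood inference under MAR also relies on a correctly specified mean model, a condition that the missing-data sentence leaves out. If those who stay to week 10 differ at baseline between the arms, a wrong slope carries part of that difference into the week-10 treatment contrast.

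**Working it through.** **Inputs.** From the article: the list of terms, the unstructured covariance, the two visits, 50 participants and r = 0.50. Assumed, because the article gives none: 25 per arm (1:1), SD 1 at each visit, residual correlation 0.6 between visits, slope pairs for weeks 6/10 as below, and logistic dropout at week 10 with a log-odds coefficient of 1 per SD and about 22 to 24% missing overall.

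**Step 1, the plan's own figure.** With r = 0.50 at both visits and equal SDs, the slopes are 0.50 and 0.50, the pooled slope is 0.50 and the error is zero. On that reading there is no problem.

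**Step 2, the pooled slope when the slopes differ.** With residual variances v6 = 1 − b6² and v10 = 1 − b10², and residual covariance c = 0.6 × √(v6 × v10), the weights are v10 − c for week 6 and v6 − c for week 10. The pooled slope is the weighted mean of b6 and b10.

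| Slopes 6/10 | v6, v10, c | Weights 6, 10 | Pooled slope | True minus pooled: week 6, week 10 |
|---|---|---|---|---|
| 0.55/0.45 | 0.698, 0.798, 0.447 | 0.350, 0.250 | 0.508 | 0.042, −0.058 |
| 0.6/0.4 | 0.640, 0.840, 0.440 | 0.400, 0.200 | 0.533 | 0.067, −0.133 |
| 0.7/0.3 | 0.510, 0.910, 0.409 | 0.501, 0.101 | 0.633 | 0.067, −0.333 |

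The pooled slope misses both visits, and misses by more at the visit with the larger residual variance. Large-sample simulation gave the same pooled slopes (0.508, 0.533, 0.632).

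**Step 3, complete data.** Randomisation follows baseline testing, so a wrong slope does not bias the contrast. Ignoring estimation of the slope, with e10 the week-10 slope error, the week-10 SE is √[(2/25) × (v10 + e10²)], against √[(2/25) × v10] with the right slope.

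- Slopes 0.6/0.4: √[0.08 × (0.840 + 0.0178)] = 0.262, against √(0.08 × 0.840) = 0.259, a ratio of 1.01. Simulation at N = 50: 0.267 against 0.263.
- Slopes 0.7/0.3: √[0.08 × (0.910 + 0.111)] = 0.286, against √(0.08 × 0.910) = 0.270, a ratio of 1.06. Simulation: 0.291 against 0.274.

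The simulated values are slightly larger because the slope also has to be estimated. Rejection at week 10 under no effect was 4.6 to 5.1% for the stated model.

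**Step 4, arm-specific dropout.** The week-10 bias is (difference between arms in completers' mean baseline) × [e10 − g × e6]. Here e6 and e10 are true minus fitted slope, and g is the fitted regression of the week-10 residual on the week-6 residual. In an arm with 24% missing under the assumed dropout model, completers' mean baseline shifts by E[p(1 − p)]/(1 − 0.24) = 0.156/0.76 = 0.205 SD.

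For slopes 0.6/0.4:

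- Dropout related to baseline in one arm only: fitted slope 0.550, so e6 = 0.050 and e10 = −0.150. Then g = (0.440 − 0.0075)/(0.640 + 0.0025) = 0.673 and the bracket is −0.150 − 0.673 × 0.050 = −0.184. Bias: 0.205 × 0.184 = 0.038 SD. Simulation: 0.039.
- Opposite directions in the two arms: fitted slope 0.555, g = 0.674, bracket −0.155 − 0.674 × 0.045 = −0.185. Bias: 2 × 0.205 × 0.185 = 0.076 SD. Simulation: 0.078.

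Simulated absolute week-10 bias in SD units (true effect zero, one million participants):

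| Dropout pattern | 0.5/0.5 | 0.55/0.45 | 0.6/0.4 | 0.7/0.3 |
|---|---|---|---|---|
| None | 0.002 | 0.001 | 0.001 | 0.001 |
| On baseline or week-6 score, alike in both arms | ≤0.003 | ≤0.003 | ≤0.005 | ≤0.004 |
| On baseline, one arm only | 0.001 | 0.020 | 0.039 | 0.079 |
| On baseline, opposite by arm | 0.001 | 0.036 | 0.078 | 0.162 |
| On week-6 score, one arm only | 0.003 | 0.007 | 0.024 | 0.056 |
| On week-6 score, opposite by arm | 0.001 | 0.021 | 0.052 | 0.115 |

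With baseline × visit added, every entry is below 0.006. The week-6 contrast was unbiased throughout. These fits used maximum likelihood; the plan names REML, which should make little difference to the estimated means.

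**Step 5, effect on error rates at N = 50.** Week-10 rejection, stated model against the model with the added term: one-arm dropout at 0.6/0.4, 5.3% against 5.2%; opposite dropout at 0.6/0.4, 6.3% against 5.9%; one-arm at 0.7/0.3, 5.3% against 6.4% (simulation noise); opposite at 0.7/0.3, 8.7% against 5.5%. Only the last case separates the two models.

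**The case against.** The case for leaving the model alone is fair in several respects.

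- It is a standard covariance-adjusted mixed model, and nothing in the article shows that the slopes differ. Two visits four weeks apart and a single planning correlation point, if anything, to similar slopes. This stands. But equal correlations imply equal slopes only if the two visit SDs are equal, and the article gives no SDs. The planning correlation is therefore neither evidence of a fault nor proof of its absence.
- A reader might infer that baseline adjustment is wrong at one visit and right at the other. It is not: with unequal slopes the pooled value misses both.
- A reader might infer that robustness under MAR fails whenever the slopes differ. For the treatment contrast this is too strong. With unequal slopes it stayed within 0.005 SD of zero when dropout worked alike in both arms. Bias needed unequal slopes together with an arm-specific dropout pattern, and it touched only week 10.
- A reader might count the shift from a chance baseline imbalance as bias. That shift averages to zero over randomisation and is already part of the SE in Step 3.
- Multiple imputation is planned above 10% missing, and a suitable imputation model would return the contrast to the unbiased complete-data case. This is a real safeguard, but only as a sensitivity analysis: the primary estimate keeps the common slope.
- The article is condensed and its list is introduced with wording that could admit further terms. Even so, it names the visit × treatment interaction and no other, so the natural reading is one common slope.

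**Conclusion.** This is a cheap improvement of minor weight, not an error in the plan. As listed, the model assumes equal baseline slopes at 6 and 10 weeks without need, and the MAR sentence leaves out the condition that the mean model be right.

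With complete data the contrast is unbiased and the price is a small loss of precision: about 1 to 2% in the SE at slopes 0.6/0.4 and about 6% at 0.7/0.3. With arm-specific, baseline-related dropout and slope differences of 0.1 to 0.2, the week-10 bias is about 0.02 to 0.04 SD (one arm) or 0.04 to 0.08 SD (opposite directions). That is small beside a week-10 SE of about 0.27 to 0.30. Larger figures need the extreme pair 0.7/0.3.

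All these sizes rest on assumed slopes, SDs, residual correlation and dropout. With equal slopes the bias is nil.

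**What to change.** Add the baseline × follow-up visit interaction to the fixed effects of the DHI and FGA models and of the similar secondary models. Extend the missing-data sentence to say that robustness under MAR also requires a correctly specified mean model.

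The cost is one line of text, one extra parameter per model and no new data. If the slopes are in fact equal, the loss of precision is small. With complete data the week-10 SE went from 0.243 to 0.244 (0.001/0.243 = 0.4%). With dropout strongly related to baseline in opposite directions, separate simulations put the loss at about 2 to 3% (for example 0.270 to 0.278, where 0.008/0.270 = 3.0%). The Data Availability section says that collected data stay blinded until completion, so the change can be fixed before results are seen.
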